#### Defining compliance

Compliance with the intervention will be estimated as the proportion of 2-week time intervals where the participant was compliant and estimated by study arm and over time. The JKT recruits must wear uniforms and will be provided with two treated uniforms. They have no alternative clothing, leading to an expected 100% compliance; compliance with clothing will not be monitored. Participants’ repellent bottles will be weighed twice weekly to estimate application rates. If a bottle contains more than 50% of the required dose, the participant will be recorded as non-compliant.

#### Descriptive analysis

Baseline characteristics of participants will be summarised by the study arm using appropriate measures of centrality and variability such as proportions, the mean and standard deviation or median and 90% central range, depending on the distribution. Clustering by combania will be considered throughout.

#### Estimates of protective efficacy

The primary outcome is the incidence of new malaria infections identified by qPCR period per person-month at risk. The incidence rate ratio (IRR) to compare study arms will be estimated using a regression model with combania as a random effect to account for the clustering. Initially, we will adopt a Poisson or negative binomial model, depending on the data distribution. The effect of the intervention over time will be investigated using interaction terms.

An unadjusted estimate will be presented, as well as an estimate adjusted for factors that are identified a priori to be potential confounders (age, region of origin, body surface area, night-time activity, use of bed nets, frequency of uniform washing).

The results will be presented as incidence rate ratios with 95% confidence intervals and *p*-values. The protective efficacy of each intervention will also be estimated as (1 – IRR) × 100%.

#### Interim analyses {21b}

An interim analysis would be unlikely to stop the trial for futility or overwhelming intended benefit because the interventions are already approved products with tested mosquito bite prevention and because the number of malaria infections may increase in tandem with conditions for mosquitoes at irregular times in the year. However, if during the trial unusual weather affects malaria transmission intensity in the area resulting in decreased malaria transmission and if an incidence substantially of lower than 0.68 is observed in the control arm, then the study may be extended to capture another malaria transmission season. An interim analysis at 6 months will determine only the number of malaria infection incidents detected and preserve the blinding of the investigators and study staff.

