### Provisions for post-trial care {30}

All recruits who will give their consent to participate will be insured for a period of 14 months (Fig. 1). The insurance will cover the 12 months of trial follow-up and 2 months after the trial ends on health issues that arise as a direct consequence of trial participation. During the trial, any participant who experiences a serious adverse event related to the study intervention will be transported to Bombo Regional Hospital. Referral to the regional hospital is to provide ancillary needs that may otherwise arise during trial participation.

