#### Implementation {16c}

The combania will be allocated to the intervention by an independent statistician, who will carry out the randomisation and retain the codes. This statistician will not be further involved in the trial. The code master list will be provided to a site manager by the statistician using email to ensure concealment. Uniforms and lotion will be assigned to combania by the study site manager following the code master list.

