### Assignment of interventions: blinding

#### Who will be blinded {17a}

In this double-blinded placebo-controlled trial, the participants, investigators and study statistician will be blinded to the allocation of interventions by a combination of intervention codes and combania codes.

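### The extension rule depends on a control-arm incidence that the stated interim does not supply and that no unblinded role is assigned to compute; a blinded pooled event count would be a better trigger

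*Protocol article*

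**What the plan says.** All references are to the protocol article.

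- **Interim analyses {21b}, trigger.** Extension is possible if unusual weather reduces transmission and "if an incidence substantially of lower than 0.68 is observed in the control arm, then the study may be extended" to take in a further transmission season. No numeric cut-off and no date for reading the trigger are given.
- **Interim analyses {21b}, output.** The next sentence describes the only planned look: at 6 months it "will determine only the number of malaria infection incidents detected and preserve the blinding of the investigators and study staff".
- **Who will be blinded {17a}.** "the participants, investigators and study statistician will be blinded to the allocation of interventions".
- **Implementation {16c}.** An independent statistician randomises and keeps the codes, but "This statistician will not be further involved in the trial". A second person also receives the list: "The code master list will be provided to a site manager by the statistician using email to ensure concealment", and "Uniforms and lotion will be assigned to combania by the study site manager following the code master list".
- **Concealment mechanism {16b}.** Each combania has its own code, so the control combania cannot be grouped from the codes alone.
- **Composition of the data monitoring committee {21a}.** None is planned; the institutional review board oversees through annual reports.
- **Sample size {14}.** The primary comparison is etofenprox uniform plus DEET against permethrin uniform plus DEET, 12 combania each. Untreated uniform plus placebo lotion has 6 combania, about 240 people, with 0.68 infections per person-year as the baseline.

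**The concern.** The trigger and the interim output do not fit together. A control-arm rate needs arm labels; a number of infections obtained with the blind intact does not carry them. The section names nobody to supply the rate and nobody to take the decision.

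If transmission does fall, the team will have to improvise. The obvious improvisation is for someone to group the control combania and report their rate to those deciding whether to extend. Set beside the overall count, that rate also shows how the three treated arms fare together against untreated uniforms, which bears on the secondary comparisons.

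The quantity is also poorly suited to its purpose. An extension is meant to rescue an under-informative trial, but the rate comes from a 6-combania arm that is not in the primary comparison.

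**Working it through.** **1. Inputs.** Stated rates per person-year: control 0.68, permethrin plus DEET 0.41, etofenprox plus DEET 0.27. Participants: 480, 480, 240, 240. Not stated, so assumed: permethrin plus placebo at 0.41 (range 0.41 to 0.68), no dropout or excluded time, two-sided 5% test, and the between-combania log-SD.

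**2. The plan's own figures, used to bound the log-SD.** For the primary comparison, SE² = 1/(480 × 0.41) + 1/(480 × 0.27) + 2 × SD²/12 = 0.0128 + SD²/6, and |ln(0.27/0.41)| = 0.418.

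- SD 0.16: SE = 0.131, power 0.892, matching the stated 89%; interval 0.51 to 0.85.
- SD 0.24: SE = 0.150, interval 0.49 to 0.88, matching the stated interval; power 0.80.

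Under this approximation no single SD gives both figures, so 0.16 to 0.24 is used as a range. (The 0.41 reproduces from 0.68 × (1 − 0.5 × 0.8) = 0.408. The 0.27 does not: 0.68 × (1 − 0.7 × 0.8) = 0.299. The stated 0.27 is used below.)

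**3. Precision of the control-arm trigger.** SE = √(1/events + SD²/6); range = 0.68 × exp(±1.96 × SE).

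| Read at | Expected control events | SD 0.16 | SD 0.24 |
|---|---|---|---|
| 6 months | 240 × 0.5 × 0.68 = 81.6 | SE 0.129; 0.53 to 0.87 | SE 0.148; 0.51 to 0.91 |
| 12 months | 240 × 0.68 = 163.2 | SE 0.102; 0.56 to 0.83 | SE 0.125; 0.53 to 0.87 |

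With no clustering at all, the 6-month range is still 0.55 to 0.84.

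**4. The pooled count.** Per year: 480 × 0.41 + 480 × 0.27 + 240 × 0.41 + 240 × 0.68 = 196.8 + 129.6 + 98.4 + 163.2 = 588, or 588/1440 = 0.41 per person-year. At 6 months: 294. With SE = √(1/events + SD²/36), the relative error at 6 months is 6.4% to 7.1%, against 12.9% to 14.8% for the control arm. At 12 months it is 4.9% to 5.7%, against 10.2% to 12.5%. That is about half the error at either time. (The formula treats the 36 combania as contributing equally, which is an approximation.)

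**5. Can the pooled count stand in for the existing trigger?** No. The control rates that give the same 6-month total of 294 are:

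- full planned effects: 0.68;
- half the planned effects: 0.51;
- no effects: 294/720 = 0.41.

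With permethrin plus placebo at 0.68 the total is 326, and the control rates are 0.68, 0.54 and 0.45. A pooled count therefore cannot tell whether control incidence is below 0.68.

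**6. What a pooled threshold might look like.** For 80% power at the planned ratio, SE must be at most 0.418/(1.96 + 0.842) = 0.149, so SE² = 0.0222. If all rates scale together, the required fraction of planned events is 0.0128/(0.0222 − SD²/6). At SD 0.16 this is 0.71, or about 419 pooled infections. At SD 0.24 it is 1.01, or about 596. The threshold depends heavily on the clustering assumption and must come from the sponsor's own simulation.

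**The case against.** Several points limit the concern.

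- **A reader might infer that the rule cannot be run without breaking the blind.** The documents do not support that. The site manager receives the code list and is not among those named as blinded. Whether the list shows arms, and whether this person counts as study staff whose blinding is kept, is not stated. A code-holder outside the blinded team could compute the rate and return only extend or do not extend. The gap is an unassigned role. The site manager is given no analytic task.
- **A reader might infer bias in the primary comparison.** None is shown. The untreated arm is outside that comparison, so its rate says nothing direct about etofenprox against permethrin.
- **Low control incidence is not enough on its own.** Unusual weather is also required, and extension is only permitted. A chance dip alone does not meet the rule. This narrows the rule but does not supply the missing rate.
- **The trigger is not tied to month 6.** That is fair, which is why both time points are shown. The imprecision remains at 12 months.
- **The interim number is not expressly pooled.** Preserved blinding makes pooled the natural reading, but it is a reading.
- **A pooled count answers a different question.** This stands: it cannot separate low transmission from high efficacy. It does measure the information available for the primary comparison, which is the better reason to extend.
- **Details such as the cut-off may sit in an analysis plan.** That covers the missing number, which is not pressed here. It does not cover a trigger and an interim output that do not match within one section.

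**Conclusion.** The point holds as a mismatch. The extension rule needs a control-arm rate, the one interim described does not provide it, and no unblinded role is assigned to compute it. The rule is not operable as written, and improvising it risks exposing arm-level data to those who decide on trial length.

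The trigger is also weak. At the upper assumed log-SD of 0.24, an observed rate anywhere from about 0.51 to 0.91 at 6 months, or 0.53 to 0.87 at 12 months, is compatible with a true 0.68. These ranges rest on an SD that the protocol does not give, and on no loss of person-time. The mismatch itself rests on the text alone.

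This is a change the sponsor should make, not a fatal flaw. The insurance term is secondary: participants "will be insured for a period of 14 months", that is, 12 months of follow-up plus 2, so an added season would probably outlast it. An amendment could deal with that.

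**What to change.** In Interim analyses {21b}, replace the control-arm trigger with a threshold on the blinded pooled number of primary infections across all 36 combania.

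- Set the threshold in advance by rerunning the power simulation for etofenprox plus DEET against permethrin plus DEET. State the minimum power and the between-combania variance used.
- Give the planned pooled count beside it: about 588 a year (0.41 per person-year) at the stated rates, assuming 0.41 for permethrin plus placebo. If the etofenprox rate is taken as 0.299 and the permethrin rates as 0.408, the total is 195.8 + 143.6 + 97.9 + 163.2, about 601. Settle the rates first.
- Apply the threshold once both rainy seasons are in. Use the 6-month count only as an early warning.
- State who takes the decision, and note that insurance cover must be extended with any extension.

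If the sponsor prefers to keep the control-arm rate, the alternative is to name an unblinded person outside the trial team who reports only extend or do not extend. That makes the rule operable but leaves its imprecision.

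The cost is one amended paragraph and one rerun of an existing simulation, with no new data. The article reports that recruitment has not begun, so the threshold can be fixed before any outcome is seen.

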#### Methods for additional analyses (e.g. subgroup analyses) {20b}

We do not plan any subgroup analysis.

#### Methods in analysis to handle protocol non-adherence and any statistical methods to handle missing data {20c}

We expect that there will be little missing data since there will be active follow-up during the trial. For all analyses, participants will be included for all time points where their data is not missing. If there is missing data, we will conduct sensitivity analyses to check that the calculations are not affected.

#### Plans to give access to the full protocol, participant-level data and statistical code {31c}

The project database containing entomological and epidemiological data will be de-identified based on local IRB requirements. The de-identified data and accompanying metadata in the Ifakara Health Institute data repository will be made available on reasonable request.

### Oversight and monitoring

#### Composition of the coordinating centre and trial steering committee {5d}

Not applicable. It is not a multicentre trial. Also, trials with minimal risks to participants do not necessarily require a data monitoring committee.

#### Composition of the data monitoring committee, its role and reporting structure {21a}

The trial is intended to examine interventions that reduce mosquito bites; permethrin, etofenprox and DEET are known already to have excellent human safety profiles [13, 15]. Trials with minimal risks to participants do not necessarily require a data monitoring committee (DMC) [44]. The trial does not examine prolonging of individual life or reduction of risk of a major adverse health outcome as do trials comparing mortality or morbidity of participants. Therefore, the trial will be minimal risk. However, the Ifakara Health Institute Institutional Review Board (IRB) will provide oversight through annual reports. The IRB comprises epidemiologists, statisticians, entomologists, social scientists and community leaders.

#### Adverse event reporting and harms {22}

The team physician will determine the relationship between any adverse event and the intervention. All adverse events will be treated as clinically indicated, and subsequent treatment will be recorded. If necessary, participants will be referred for special care at the local hospital. Study clinicians who determine that an AE/SAE (adverse event or severe adverse event) is intervention related and that stopping intervention is clinically indicated will stop the study intervention. All adverse events will be reported to the IRB. Adverse events will be recorded, and descriptive analysis of adverse events will be reported as part of the publication arising from the trial.

#### Frequency and plans for auditing trial conduct {23}

The trial will be overseen by the IHI Quality Assurance Unit, which will audit the trial protocol and all critical phases, i.e. enrolment, allocation of intervention, the study report and study archive.

#### Plans for communicating important protocol amendments to relevant parties (e.g. trial participants, ethical committees) {25}

The trial team is responsible for all amendments to the protocol. The fundamental amendments to be reported will include the change to the protocol that may modify study objectives, study procedures, inclusion criteria, sample sizes, trial outcome, analysis plan and blinding and other changes which may impact on the conduct of the study by either affecting the safety of trial participants or the scientific validity, scope or ethical thoroughness of the trial or bringing any potential benefit of the participants. Any of these amendments will be agreed upon by the study team and be approved by the IHI IRB and the National Institute of Medical Research (NIMR-Tanzania) and changes will be updated into the trial register. In addition, the IHI Quality Assurance Unit will be notified. When an old protocol is updated to a newer version, the new version of the protocol gets another number that identifies the protocol version and the date. This will help to track histories of amendments and marks the latest protocol version.

### Dissemination plans {31a}

Final trial results will be disseminated to stakeholders at the Tanzania People’s Defence Force (TPDF) and the scientific community via publication of study findings in open-access, peer-reviewed journals and international conference forums. In addition, yearly progress reports will be distributed to key stakeholders. All researchers and technical staff who contribute to the research will be authors on any publications arising from the research as per the Vancouver Protocol. The results of this trial are intended to be disseminated regardless of the magnitude or direction of effect.

## Discussion

Better ways to protect military personnel from malaria on active duty are required. Findings from the proposed trial will provide knowledge to improve malaria prevention among military personnel. We will provide information on which combination of interventions is most effective and may reduce unnecessary costs to institutions, such as the cost of topical repellents. Identifying factors for non-adherence may improve the design of future bite prevention interventions.

The trial will evaluate the impact of interventions in an active duty environment. The results may be relevant to other occupations with exposure to an increased risk of mosquito bites and vector-borne disease, including forest workers, guards and miners, loggers and rubber tappers [45]. If beneficial, other potential users could include visitors to endemic regions [46], relief workers [47] and refugees [48].

Insecticide-treated clothing may also protect wearers from day-biting mosquitoes, such as *Aedes aegypti*, which are currently increasing rapidly in Tanzania [49], as well as other arthropods that engage in nuisance biting. This trial will not test efficacy against dengue but may generate data needed for Tanzanian registration of insecticide-treated clothing that could have benefits for multiple vector-borne diseases. Etofenprox has not previously been put into a trial that estimates efficacy in combination with another repellent. Due to low toxicity and environmental safety [50], vendors may find a new niche in the community for impregnating clothes with the repellent.

The study involves a group of young people who, because they must wear their uniform as part of their job, will be more likely to comply effectively with the intervention than would the general population. While this is necessary to determine the true effect of insecticide-treated clothing to reduce disease under controlled conditions, the results may overestimate the effectiveness of the intervention for the general population. However, it is likely that compliance among military personnel will be similar to that among other users whose occupations require them to wear uniforms, such as guards, miners and nurses. This may influence generalizability of the findings, as the effectiveness of any personal protection method is dependent on compliance. Data generated from the comparison of the intention-to-treat and per-protocol analyses [51–53] will give useful information about compliance among the troops.

## Conclusion

Interventions that are protective when vectors are active and when humans are away from their houses need to be developed [54, 55]. This study will estimate the impact of insecticide-treated clothing and DEET lotion on reducing malaria infection transmission in military personnel.

## Trial status

Protocol version: BIT014_URCT_PR_v12

Protocol date 30/09/2020

Participant recruitment has not begun.

## Abbreviations

ACU: Army combat uniform
BIT: Bagamoyo Insecticide Testing
CO: Commanding officer
DEET: *N*,*N*-Diethyl-meta-toluamide
DMSNS: Director of Medical Services National Service
DNA: Deoxyribonucleic acid
DWFP: Deployed War-Fighter Protection
EDTA: Ethylenediaminetetraacetic acid
EPA: Environment Protection Agency (US)
ETU: Etofenprox-treated uniforms
GLMMs: Generalized linear mixed models
HQ: Headquarters
HsRNaseP: Human ribonuclease P
IHI: Ifakara Health Institute
IRB: Internal Review Board
IRR: Incidence rate ratio
JKT: Jeshi la Kujenga Taifa (National Service)
LOD: Limit of detection
MDA: Mass drug administration
NIMR: National Institute of Medical Research (Tanzania)
NOAEL: Non-observed adverse effect level
NTC: Non-template control
ORP HRPO: Office of Research Protections Human Research Protection Office
PCR: Polymerase chain reaction
PfvarATS: *Plasmodium falciparum* variant ATS
PR: Protocol
PTU: Permethrin-treated uniform
qPCR: Qualitative PCR
QC: Quality control
RNA: Ribonucleic acid
RDT: Rapid diagnostic test
RNaseP: Ribonuclease P
TPDF: Tanzania People’s Defence Forces
USAMRMC: United States Army Medical Research and Materiel Command
